## Abstract

Research has shown that physical activity programs led to improvements in children with Attention Deficit Hyperactivity Disorder (ADHD). However, no study evaluating the impact of a physical literacy (PL) program has been conducted. This study aims to examine PL and the effects of an after-school PL program on Health-related quality of life (HRQoL) and ADHD symptomatology including quality and sustained attention. A parallel-group randomised controlled trial will be conducted assessing PL, HRQoL and ADHD symptomatology, both at the beginning and the end of the PL after-school program implementation. The program will last 4 weeks, including two sessions per week lasting 55 min. Sessions will be divided into several parts: greeting (5 min), block I (20 min), block II (20 min) and relaxation and feedback (10 min). Block I will focus on the acquisition of content that contributes to the development of the domains of knowledge and understanding and daily activity; and block II, in addition to favouring physical competence, will seek to improve motivation. If this program proves its effectiveness, it could be an alternative to be included in educational systems, representing a scientific breakthrough regarding physical activity adherence and inactivity-related disease prevention, HRQoL and management of ADHD-associated symptomatology.

## 1. Introduction

Attention Deficit Hyperactivity Disorder (ADHD) is a neurodevelopmental disorder characterised by the presence of persistent patterns of inattention and/or hyperactivity and impulsivity; then, ADHD can interfere with social, academic and occupational functioning [1]. ADHD begins in childhood and can continue into the teen years and adulthood [2]. Whatever the clinical presentation of ADHD (i.e., primarily inattentive, primarily hyperactive/impulsive, mixed) a wide range of negative outcomes related to ADHD in children are recognised, including poorer life satisfaction, quality of life, and lower health outcomes compared to individuals without ADHD [3,4]. Furthermore, they may experience impairments of emotional regulation and social competence, which may compromise their integration with peers and encourage disruptive behaviours. Figures on ADHD prevalence have varied over time, although ranges of 5–7% in children and adolescents are commonly reported [5,6]. Furthermore, as in other neurodevelopmental disorders, their prevalence in boys is significantly higher than in girls, although gender bias in diagnostic criteria has been suggested [7].

Physical literacy (PL) is defined as the motivation, confidence, physical competence, knowledge and understanding to value and participate in a physically active lifestyle [8]. PL includes physical, cognitive, social and affective dimensions measures [9], but it is also a factor that can help to increase Physical Activity (PA) levels (PAL) [10,11]. Moreover, PL is a multidimensional construct which defines an individual’s ability to perform PA moving competently and with attitude, being used regarding physical and mental health throughout life [12]. There is evidence that PL is correlated with different health indicators at school age, including improved health-related quality of life (HRQoL) [9].

PL influence on schoolchildren with ADHD’s HRQoL has not yet been studied. However, several studies indicate that PA may contribute to HRQoL improvement, achieving greater benefits at higher PAL [13,14]. Physical competence is lower in children with ADHD compared to typical children, which may be explained by attention difficulties while acquiring motor skills [15]. Attention problems are a major issue for ADHD, and require proper diagnosis and management [16,17,18]. PA’s benefits have been observed in sustained attention and the quality of attention [19,20,21,22].

Then, considering the PL influence on increased PA, PL may contribute to HRQoL improvement as well as to the quality and sustained attention of schoolchildren with ADHD. There is preliminary evidence that a PA program may improve the cognitive functions and functioning of children with ADHD [23], including attention issues [24,25]. Additionally, PA impacts the mental health of children with ADHD [26], as they show poorer PAL compared to typically developing children [26,27]. Therefore, this study aims to (1) assess the PL level in children and adolescents with ADHD in Spain; and (2) improve PL and consequently HRQoL and ADHD symptomatology, including quality and sustained attention, through a PL program based on PA improvement, motivation, education and healthy lifestyle habits.

## 2. Materials and Methods

### 2.1. Design

A randomized controlled trial employing a parallel-group design will be implemented, including a 4-week intervention phase. Baseline assessments will be administered prior to commencing the intervention, followed by post-intervention evaluations immediately upon its completion. Participants will be randomly assigned to the experimental or control group. The study will be reported following the SPIRIT Statement and the TIDieR Checklist [28,29].

### 2.2. Ethics

The Ethics Committee of the University of Extremadura proceeded to provide the ethical approval needed to develop the present research project, the assigned approval number being 33/2023. In this sense, the study adheres to the revised guidelines of the Declaration of Helsinki, which were amended by the 64th General Assembly of the World Medical Association (Fortaleza, Brazil, 2013) and the Law 14/2007 on Biomedical Research. Furthermore, the study has been properly registered in the Australian New Zealand Clinical Trials Registry under the following Registration Number: ACTRN12623000389606p (accessible at https://www.anzctr.org.au/, accessed on 1 June 2023).

### 2.3. Sample Size

An a priori sample size computation was carried out using the G*Power software 3.1.9.4 (Kiel University, Kiel, Germany), selecting the One-way ANOVA statistical test, that allows the comparison between the means of two independent groups to determine whether there will be evidence that the associated population means will differ significantly. Therefore, considering a significance level of 0.05 (alpha), a 0.02 beta risk, and assuming a large effect size f of 0.4, a total of 52 participants (being 26 subjects included in both experimental and control group) will be sufficient in order to attain a minimum power of 80%.

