### 2.4. Randomization and Blinding

Participants will be part of either the experimental (EG) or control group (CG) by following a random assignment process. Prior to participant enrolment (1:1), a randomization sequence will be generated by the free resource Research Randomizer software (version 4.0, Geoffrey C. Urbaniak and Scott Plous, Middletown, CT, USA; accessible at http://www.randomizer.org, accessed on 15 January 2023) [30]. The group assignment process will be conducted by a designated member of the research team who will not have active involvement in the trial. The allocation of participants to either the experimental or control group will be recorded in a computer file secured with a password to ensure confidentiality and data integrity. Neither the outcome assessors nor the data analysts will be aware of the participant’s group assignment.

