### 2.8. Statistical Analysis

The Statistical Package for the Social Sciences SPSS (IBM SPSS Statistics, Version 25.0. Armonk, NY, USA) will be used for statistical analyses and computations. Data will be presented as means and standard deviation (SD). The Kolmogorov–Smirnov test and Levene’s test will be applied to check the normality and homogeneity of data. After that, a group × time repeated measures ANOVA will be employed to analyse the impact of the intervention on the various dependent variables. Effect size will also consider Cohen’s d, accompanied by a 95% confidence interval. Statistical significance will be determined for the within-group effect of time and the interaction group × time. Alpha significance level will be established at *p* ≤ 0.05.

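### The 80% power in section 2.3 is computed for a one-way comparison with all 52 children analysed; it is not shown for the group-by-time interaction and has no reserve for loss

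*Protocol article*

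**What the plan says.** Section 2.3 (Sample Size) names the sizing test, "selecting the One-way ANOVA statistical test, that allows the comparison between the means of two independent groups", and its inputs: "considering a significance level of 0.05 (alpha") and "assuming a large effect size f of 0.4". The resulting size is "a total of 52 participants (being 26 subjects included in both experimental and control group"). Of this number the section claims that it "will be sufficient in order to attain a minimum power of 80" per cent. It gives no pre-post correlation and no allowance for children without a second assessment, and it does not say which score f standardises. Section 2.4 sets 1:1 allocation.

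Section 2.1 (Design) has two assessments, at baseline and straight after the four-week programme. Section 2.8 (Statistical Analysis) says that a group-by-time "repeated measures ANOVA will be employed" for the various dependent variables, with significance judged on the time effect and the interaction. A comparison of the two groups at a single time is not among the tests listed there.

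**The concern.** With two assessments, the interaction test is the same as a two-group test on change scores (post minus baseline). The spread of a change score depends on the pre-post correlation, so a power figure for a comparison of group means at one time does not carry over to it unless that correlation has a particular value. Section 2.3 also attaches the word minimum to the smallest even total that reaches 80%, so any child who does not enter the analysis uses up the margin.

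At stake is how a null result would be read. If the article says that power was at least 80% for a large effect, readers will take a non-significant interaction as evidence against such an effect. Under some plausible inputs the power would be nearer two in three.

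**Working it through.** **Inputs.** From section 2.3: alpha 0.05, f = 0.4, two groups, N = 52. From section 2.4: equal arms. From sections 2.1 and 2.8: two assessments and the interaction test. Assumed, because the article gives neither: pre-post correlation ρ from 0.3 to 0.7, and 42 to 52 children analysed. Section 2.3 also states "a 0.02 beta risk", which would mean 98% power and 104 children; 52 matches a beta of 0.20, so 80% is taken as the target here.

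**Step 1: reproduce the article's figure.** For two equal groups f = d/2, so f = 0.4 is a difference of 0.8 SD. Power comes from the noncentral F distribution with 1 and N − 2 degrees of freedom and noncentrality λ = N·f². At N = 52, λ = 52 × 0.16 = 8.32 and power is 80.7%. At N = 50, λ = 8.00 and power is 79.1%. So 52 is the smallest even total reaching 80%, and the article's number is right for the test it names.

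**Step 2: the interaction, if f refers to post scores.** With equal SDs at both times, the SD of the change score is SD·√(2(1 − ρ)). Hence f(change) = 0.4/√(2(1 − ρ)), and λ = N·f(change)². At ρ = 0.3, for example, f(change) = 0.4/√1.4 = 0.338, and λ = 52 × 0.16/1.4 = 5.94.

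| ρ (assumed) | f(change) | 52 analysed | 44 analysed | 42 analysed |
|---|---|---|---|---|
| 0.3 | 0.338 | 66.7% | 59.1% | 57.1% |
| 0.4 | 0.365 | 73.3% | 65.8% | 63.7% |
| 0.5 | 0.400 | 80.7% | 73.6% | 71.6% |
| 0.6 | 0.447 | 88.5% | 82.6% | 80.7% |
| 0.7 | 0.516 | 95.5% | 91.7% | 90.4% |

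Here 44 analysed is about 15% loss (44/52 = 0.846) and 42 about 20% (42/52 = 0.808). Power equals 80% at ρ of about 0.49 with no loss, 0.54 with 10% loss and 0.60 with 20% loss.

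**Step 3: the interaction, if f refers to change scores.** Then ρ drops out and only the number analysed matters: 80.7% at 52, 79.96% at 51, 79.1% at 50, 76.5% at 47, 73.6% at 44 and 71.6% at 42. The dip at 51 is negligible; from 50 downwards the figure is plainly under 80%.

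**Step 4: the alternative analysis.** Adjusting the post score for baseline reduces the residual SD by √(1 − ρ²), so f(ANCOVA) = 0.4/√(1 − ρ²), with one further degree of freedom spent (N − 3).

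| ρ (assumed) | 52 analysed | 44 analysed |
|---|---|---|
| 0.3 | 84.2% | 77.5% |
| 0.4 | 87.0% | 80.7% |
| 0.5 | 90.4% | 84.9% |

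At these correlations each figure is above the interaction test's: 84.2% against 66.7% at ρ = 0.3 with 52 analysed, for example.

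**The case against.** The best defence is that nothing is miscalculated. The stated inputs give 52, and a one-way ANOVA on change scores is the interaction test. If f = 0.4 was meant for change, the sizing test and the planned test coincide. That reading is open, because section 2.3 does not say which score it means. It removes the dependence on ρ, but not the lack of reserve.

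A reader might go further and infer that the trial is underpowered. The documents do not support that. They give neither a correlation nor a loss rate, and nothing in them points to a correlation below 0.5. At 0.6 or above the interaction keeps at least 80% even with 42 analysed.

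It is also fair to say that the article does not define its analysis set. That a child without a post score drops out is inferred from how a standard repeated measures ANOVA works. Missing-data handling may well sit in a fuller document, and its absence here is not criticised. What stands is that section 2.3 itself attaches a minimum to a calculation which, as written, is not tied to the test in section 2.8.

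**Conclusion.** The point holds as a gap between the power claim and the planned test. The 80% is correct for a one-way comparison with all 52 analysed, but it is not demonstrated for the interaction. On the post-score reading the claim needs a correlation of about 0.49 or more with no loss at all. On the change-score reading it fails once two children, under 4% of the sample, are not analysed. Whether the trial will in fact fall short cannot be settled from the article, since it turns on the correlation, the loss and the scale of f. All correlations and loss rates used here are assumptions, as is equal SD at the two assessments. This should be corrected, but it does not stop the trial from running.

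**What to change.** Rewrite the paragraph in section 2.3 for the analysis actually used. State which score f refers to, the assumed pre-post correlation with a range, and the number expected to be analysed as distinct from the number enrolled. Drop the word minimum, or give the loss up to which 80% holds.

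Preferably, also change section 2.8 so that the group comparison is an ANCOVA of the post score adjusted for its baseline value. A possible wording: *for a difference of 0.8 SD in the post score, two-sided alpha 0.05 and an assumed pre-post correlation of 0.4, power is 87.0% with 52 children analysed and 80.7% with 44 (about 15% loss); at a correlation of 0.3 these are 84.2% and 77.5%*. The last figure should stay in the text, because ANCOVA does not secure 80% at low correlation with 15% loss.

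The cost is one paragraph, plus one sentence in section 2.8 if ANCOVA is adopted; the baseline is already measured. If the repeated measures ANOVA is kept, section 2.3 should give the break-even correlations from the working. If 52 analysed is the aim, enrolment would be 52/0.90, rounded up to 58, for 10% loss; 52/0.85, rounded up to 62, for 15%; or 52/0.80 = 65 for 20%.

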### 2.4. Randomization and Blinding

Participants will be part of either the experimental (EG) or control group (CG) by following a random assignment process. Prior to participant enrolment (1:1), a randomization sequence will be generated by the free resource Research Randomizer software (version 4.0, Geoffrey C. Urbaniak and Scott Plous, Middletown, CT, USA; accessible at http://www.randomizer.org, accessed on 15 January 2023) [30]. The group assignment process will be conducted by a designated member of the research team who will not have active involvement in the trial. The allocation of participants to either the experimental or control group will be recorded in a computer file secured with a password to ensure confidentiality and data integrity. Neither the outcome assessors nor the data analysts will be aware of the participant’s group assignment.

### 2.5. Participants

In order to be eligible for inclusion in this project, participants must meet the following criteria: (1) having an ADHD clinical diagnosis; (2) no co-morbidities with other neurodevelopmental or psychiatric disorders; (3) aged between 8 and 16 years; (4) not suffering from pathologies that contraindicate the practice of exercise or limit the execution of the PA program; (5) and having authorisation from parents or legal guardians.

### 2.6. Intervention

**Experimental group:** an after-school intervention based on the development of the PL domains will be implemented based on a previous study [31]. Considering the duration of previous PA interventions in this population [32], a period of 4 weeks, with 2 sessions per week of 55 min duration, was established. Sessions will be divided into several parts, starting with a 5 min greeting and exchange of daily experiences, 20 min for block I, 20 min for block II, and 10 min for relaxation and feedback. Aspects such as the adequacy of an attractive playroom favour the acquisition of intrinsic motivation [33].

Block I: activities for developing participants’ knowledge and understanding of concepts, as well as attitudes, regarding both healthy lifestyle habits and PA will be carried out through the “card relay race” activity, whereby participants will be organized into teams and positioned in rows. Each member of the team will be provided with a card (model) to be held in his/her hand and will run to a table located about 30 metres away. Once there, he/she will find a series of cards similar to his/her own (stimuli) and will place the card in his/her hand on top of one of the cards on the table that corresponds to his/her own (i.e., look for the stimulus that corresponds to his/her model). Subsequently, he/she will do the race back so that the next partner can come out. Each week, the contents of the activity will be different (healthy lifestyle habits, how to be active?, kinds of fitness and type of sports). Each session, there will be an initial brief explanation of the content to be developed that day (Figure 1). This activity, adapted from a previous study [34] is intended to improve attentional functioning as well as to acquire knowledge about healthy lifestyle habits, while at the same time practising physical activity. Thus, it will contribute to two fundamental pillars of PL such as knowledge and understanding, daily activity and physical competence.

Block II: The second block will be based on active play, essential for values and attitudinal content transmission, as well as on the stimulation of social and civic relationships with others. In line with previous studies on ADHD children [35,36,37], different ball games, including multi-jumping and throwing games, will be performed. Figure 1 shows the games that will be played each week, and their description is provided in PlaySport (http://www.playsport.net, accessed 25 January 2023). The games employed in this study will incorporate elements of both cooperation and competition, as these components have been established to provide motivational benefits [38]. Furthermore, in order to enhance motivation and self-assurance, inclusivity among participants, considering both gender and ability, will be guaranteed by adapting all activities to enable equal learning and active engagement for everybody. Group formation strategies and cooperative activities with a shared objective or purpose will be utilized to promote collective accomplishment [39]. Participants’ active engagement will be ensured by verbal feedback provided by activity coordinators, facilitating their involvement and fostering the development of relationship-infused self-efficacy (RISE) [40,41]. PA and games in children with ADHD can improve perceptual and cognitive functions [42]. Therefore, for the activities that will be developed in the second block, we will try to ensure that they participate in the activities for the mere pleasure of participating and not for a specific result.

For safety reasons, the heart rate will be monitored by the instructor during the session. Participants will be informed at the beginning of the intense efforts about the possibility of raising their hand in case they are not feeling well and need to rest until they recover. Finally, they will be given time at the end of each session to express their opinions [39].

**Control group:** Participants will continue with their usual after-school activities.

### 2.7. Measures

PL and body composition will be evaluated through a variety of tools. Prior to conducting the initial measurements, participants will undergo a familiarization phase designed to acquaint them with the various instruments and assessments incorporated within this study.

Socio-demographic data. Participants’ parents or legal guardians will provide socio-demographic data. The informed consent form will be accompanied by a sociodemographic questionnaire which will include age, gender, type of school (public or private), socioeconomic status, other diagnoses, medication, school year, reinforcement at school, and therapies. These data will only be considered at baseline.

The rest of the measures will be taken at baseline and the end of the intervention and will be carried out by the participants (Figure 1).

(1). Physical Literacy. PL level will be assessed using the Canadian Assessment of Physical Literacy (CAPL-2) [43], from which there is also a preliminary validation in adolescents aged 12 to 16 years old [44]. The CAPL-2 employs a numerical scoring system ranging from 0 to 100 points, with 0 representing the lowest possible value and 100 denoting the highest achievable score. This assessment encompasses four distinct domains: (1) daily physical activity behaviour; (2) physical competence; (3) motivation and confidence; and (4) knowledge and understanding. The different domains will be assessed through a combination of concrete tests and assigned a corresponding score, as outlined below:

a. Daily activity behaviour. The total score for this domain will comprise two components: step counts data derived from an activity wristband (Xiaomi mi Band 3, Xiaomi Corporation, Beijing, China) as a feasible and valid alternative to the research-grade accelerometers [45], which will record the number of steps taken over a full week, and a self-reported inquiry concerning the frequency of engaging in at least 60 min of PA per day. Regarding the total score, it will be determined by combining the score derived from the recorded step count and the score attributed to the individual responses on the weekly PA performed.

b. Physical competence. The scores of the following three components will be combined in order to obtain the ultimate score for this domain:

*I. The Plank test* (30) consists of maintaining the plank position for as long as possible. The total time that the participant held this posture will be taken for the evaluation.

*Ⅱ. Progressive Aerobic Cardiovascular Endurance Run* (PACER) test [46] for assessing cardiorespiratory competence will be used. It involves a 20-m shuttle run (out and back) conducted in response to acoustic signals that define each test-stage intensity. The last stage completed by the participant will be taken for the evaluation.

*Ⅲ. Canadian Agility and Movement Skill Assessment* (CAMSA) [47] will evaluate the participants’ motor skills through employing an agility circuit that comprises various tasks, involving throwing, jumping, and other movements. The time taken to perform the test and the quality of the execution of the movements will be given a score.

c. Motivation and confidence. The CAPL-2 motivation and confidence questionnaire will be used [43]. Thus, participants’ self-confidence in their ability to engage in PA, as well as their motivation towards being physically active, will be evaluated. The scoring will involve the summation of four distinct dimensions, each evaluated on a scale of 1 to 7.5 points: intrinsic motivation, competition, predilection, and appropriateness. Hence, the total score for this domain will range from 1 to 30 points.

d. Knowledge and understanding. Participants’ knowledge about PA will be evaluated in accordance with this domain. [43]. The scoring will be derived from a questionnaire provided in the CAPL-2 manual, which comprises five questions in total. Four of these questions will be in multiple-choice format and scored on a scale from 0 to 1. The fifth question will involve completing missing gaps in a story and will be rated from 1 to 6.

The questionnaires will be filled in the Spanish version [48] following a previous study [49].

(2). Health-Related Quality of Life. It will be assessed using the Child health utility 9D (CHU9D) [50]. The CHU9D comprises a self-report instrument, which must be completed by the child or adolescent, as well as a proxy-report questionnaire completed by the caregiver. It is based on nine items that assess the current state of the child or adolescent across multiple domains, including worry, sadness, pain, tiredness, discomfort, school, sleep, daily routine and activities, reflecting their subjective experience. Each item presents five possible response options, scored on a scale ranging from 1 to 5.

(3). ADHD Symptomatology. The Attention Deficit Hyperactivity Disorder Test (ADHDT) will be used. This tool is designed to identify and assess ADHD from ages 3–23 years [51]. It consists of 36 items in three subscales: (a) hyperactivity, (b) inattention and (c) impulsivity. The total score ranges from 0–72, with higher scores indicating greater and more severe ADHD-related symptomatology.

(4). Quality of attention and sustained attention. It will be assessed based on the Magallanes Scale of Visual Attention (EMAV) [52]. This is used to identify the presence of ADHD and to assess the intensity and impact of the symptomatology in each case. The EMAV scale evaluates the ability to focus attention (Quality of Attention, QA) and to maintain attentional effort over some time (Sustained Attention, SA), as well as stability or performance over a relatively long time. Children should look for and identify figures identical to the model presented. For 8-year-olds, the VAS-1 will be used, where 720 possible figures are presented, of which 140 are identical to the model, and the maximum time to complete the task is 6 min. For children between 9 and 16 years of age, the EMAV-2 will be completed, where 1820 figures are presented, 340 being identical to the model, and the maximum time to complete the task is 12 min. Children’s omissions and errors will be counted to assess their sustained attention and impulsivity, respectively. Their successes are transformed into centiles following the instructions in the scale manual and using the EMAV TIPI-SOFT software [53], to obtain their level of attentional quality.

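### Scoring the PACER by the last completed stage discards 20-m lengths and adds rounding noise to the pre-post change; the loss of power depends on figures the article does not give

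*Protocol article*

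**What the plan says.** Section 2.7 describes the PACER thus: "It involves a 20-m shuttle run (out and back) conducted in response to acoustic signals that define each test-stage intensity". A stage is therefore an intensity level, and performance accumulates in 20-m lengths. The scoring rule follows: "The last stage completed by the participant will be taken for the evaluation". The article nowhere says that lengths are counted, and it does not give the number of lengths per stage or the conversion of a PACER result into CAPL-2 points.

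The PACER is one part of the physical competence domain: "The scores of the following three components will be combined in order to obtain the ultimate score for this domain". The other two parts are scored more finely: the plank on total time held, and the CAMSA on time and quality of movement.

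Section 2.6 sets the interval between measurements: "a period of 4 weeks, with 2 sessions per week of 55 min duration, was established". Section 2.8 sets the comparison: "a group × time repeated measures ANOVA will be employed to analyse the impact of the intervention on the various dependent variables". Section 2.3 plans "a total of 52 participants (being 26 subjects included in both experimental and control group").

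**The concern.** A child who improves by a few lengths without finishing another stage is scored as unchanged. A child who stopped just short of a stage end needs only one more length to gain a whole stage. Each visit's score is rounded down to a stage boundary, so the change score carries rounding error from both visits.

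With two time points, the group × time test is a comparison of mean change between groups. Extra variance in the change lowers the power of that comparison. The intervention is eight sessions over 4 weeks, so the gain to be detected may be only a few lengths, similar in size to a stage. Lengths that are not written down on the day cannot be recovered later, whereas the stage can always be worked out from the lengths.

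**Working it through.** **Step 1. The plan's own sample size.** Section 2.3 gives "considering a significance level of 0.05 (alpha), a 0.02 beta risk, and assuming a large effect size f of 0.4", with 26 per group for 80% power. For two equal groups d = 2f = 2 × 0.4 = 0.8. The exact two-sided t test at 0.05 gives power 0.807 with 26 per group and 0.791 with 25. The stated 52 therefore reproduces at 80% power. (The printed beta of 0.02 would mean 98% power and 52 per group; 52 in total fits a beta of 0.20. That is a separate matter.)

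**Step 2. What the rule does to one child.** Assume 1-minute stages rising by 0.5 km/h. Lengths per stage = speed in km/h × 1000 / 60 / 20. This gives 6.7 at 8.0 km/h, 7.1 at 8.5, 7.5 at 9.0, 7.9 at 9.5, 8.3 at 10.0 and 8.75 at 10.5, or about 7 to 9 lengths. With stages of 7, 8, 8, 8 and 9 lengths, the stage ends fall at 7, 15, 23, 31 and 40.
- From 16 to 22 lengths: stage 2 both times, change 0.
- From 22 to 23 lengths: stage 2 to stage 3, change +1.

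For a child whose starting point within a stage is arbitrary, a gain of g lengths (g less than the stage width w) moves the score with probability about g/w. With w = 8, that is 25% for 2 lengths and 50% for 4.

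**Step 3. What it does to the group mean.** Because children start at different points within a stage, these cases average out. In a simulation with mean 30 lengths, SD 10 to 20, pre-post correlation 0.7 to 0.9 and w = 4, 8 or 12 (all assumed), stage scoring kept 97% to 100% of the mean group difference. The loss is therefore noise.

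**Step 4. What it does to power for the PACER alone.** Rounding to steps of w adds a variance of about w²/12 at each visit, so w²/6 to the change. With w = 8 this is 64/6 = 10.67. Set the gain at 0.793 × SD of change, which gives 80% power on lengths with 26 per group. The standardised effect on stages is then 0.793 × √[SD² / (SD² + 10.67)]. At SD = 4, for example, this is 0.793 × √(16 / 26.67) = 0.614, and power is 0.58.

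| SD of change (lengths) | Gain assumed (lengths) | Power on stages, formula | Power on stages, simulated |
|---|---|---|---|
| 3 | 2.4 | 0.48 | 0.44-0.49 |
| 4 | 3.2 | 0.58 | 0.54-0.60 |
| 6 | 4.8 | 0.69 | 0.66-0.70 |
| 8 | 6.3 | 0.74 | 0.72-0.75 |
| 10 | 7.9 | 0.76 | 0.74-0.77 |

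The simulation used 1-minute stages starting at 8.0 or 8.5 km/h, a baseline mean of 15 to 30 lengths and a baseline SD of 8 to 14. Power on lengths was about 0.78 to 0.82 throughout.

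**Step 5. Sensitivity to stage width.** In the step 3 simulation, where the SD of change runs from about 4.5 to 15.5 lengths and d = 0.8 on lengths, power on stages was 0.76-0.80 for w = 4, 0.63-0.79 for w = 8 and 0.48-0.77 for w = 12.

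**Step 6. Dilution in the domain score.** As an illustration, take three uncorrelated, equally weighted components with equal standardised gains and 80% power for their sum. Each component then has d = 0.793/√3 = 0.458. With PACER rounding at w = 8, the sum has d = 3 × 0.458 / √(3 + 10.67/SD²). Power is 0.72 at SD 4, 0.76 at SD 6 and 0.79 at SD 10.

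**The case against.** The strongest reply concerns size and target.

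**Size.** The article gives no lengths per stage, SD of change or expected gain. The large losses need a small SD of change. With a baseline SD of 8 to 14 and correlation = 1 − SD of change² / (2 × baseline SD²), an SD of change of 3 implies a pre-post correlation of 0.93 to 0.98, and an SD of 4 implies 0.88 to 0.96. That is very high repeatability for an effort-dependent test in children with ADHD. This stands, and it is why the whole range is shown. The other end has its own demands: at an SD of change of 8 to 10, the assumed gain is 6.3 to 7.9 lengths from eight sessions. The documents do not settle where the trial lies.

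**Target.** The article does not name the PACER as a separate endpoint, and the points conversion is not shown. If the conversion itself groups results, a finer raw count may help the combined score less than step 6 suggests. This also stands.

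Two stronger readings are tempting, and the documents support neither.
- A reader might infer that the score mainly records how near a child started to a stage boundary. That can describe one child, as in step 2, but the analysis compares group means, and these are almost preserved.
- A reader might take the Introduction's statement, "Physical competence is lower in children with ADHD compared to typical children", to mean that many children will stop in the first few stages. The same sentence relates the lower competence to attention difficulties in learning motor skills, not to aerobic endurance, and the age range of 8 to 16 years suggests a wide spread of performance.

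None of this gives a reason to prefer the coarser score.

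**Conclusion.** The point holds as a loss of precision. The rule is stated outright, so it is not a detail left to a fuller document. As written, it discards within-stage performance at both visits without materially biasing the mean group difference.

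For the PACER analysed alone, the loss from about 80% power is roughly 20 to 35 points if the SD of change is 3 to 4 lengths, about 12 points at 6, and about 3 to 8 points at 8 to 10. This rests on assumed 1-minute stages, 26 per group and a gain chosen to give about 80% power on lengths. For the physical competence domain, the illustration gives a loss of about 1 to 8 points for SDs of 10 down to 4. The CAPL-2 total covers three further domains, so the effect there should be smaller still.

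A reader might conclude that the trial cannot show a 4-week fitness gain. The documents do not show that. They show an avoidable loss whose size is uncertain.

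**What to change.** In section 2.7, replace the PACER scoring sentence with one to this effect: the total number of 20-m lengths completed before stopping will be recorded, and will be used for the PACER component score and for any group comparison of the PACER; the stage reached will be reported descriptively. State, or refer to, the conversion from lengths to CAPL-2 points.

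The cost is one sentence in the protocol and one extra number on the test form. No further test or visit is needed. The change has to be made before baseline testing, because unrecorded lengths cannot be reconstructed from a stage.
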